### Recruitment

GP practices from three primary care networks (*Academic General Practitioner Development Network of UMCG*, *Julius General Practitioners Network of University Medical Center Utrecht* and *Extramural Leiden University Medical Center Academic Network*) and from the study team’s network are invited to participate by email. Participating GPs and GP trainees will recruit eligible children during office-hour consultations. Additionally, GP assistants will perform a monthly search of the primary care electronic health records (EHRs) of enlisted children using selected International Classification of Primary Care (ICPC) codes to identify and invite eligible children who have been missed by the GP (Supplementary 1).

Figure 3 outlines the recruitment process of children. During or after the consultation, the GP informs eligible children and/or parents about the study and asks consent to share contact and consultation data with the study team via an electronic case report form (CRF).

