**Fig. 3 Fig3:**
[figure not shown]
Recruitment process including data collection timeline. Anonymised baseline data (age, sex, date of baseline consultation, and randomisation group) will be collected for children who meet the inclusion criteria but do not provide consent to share contact details, or who object to participation after contact

Upon retrieval of the contact and consultation data, the study team sends an email to the parent or child, including a patient information letter and informed consent form (Supplementary 2). Patients provide written consent for participation in the study, which includes completing questionnaires, and provide separate consent for collecting relevant data from the child’s EHR. If there is no response within seven days, the study team follows up by phone to provide further study details and to answer any questions.

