### Randomisation, allocation and blinding

GP practices are randomly allocated to the intervention or control group using computer-generated 1:1 permuted-block randomisation with randomly varying block sizes, with stratification based on practice size (above or below 5000 patients). The randomisation is performed by an independent methodologist ([name], PhD). Blinding of GPs and patients is neither feasible nor appropriate in this pragmatic study [27]. Additionally, blinding of outcome assessors is not possible. However, data analysis will be conducted blinded to group allocation, meaning that the data analysts will be unaware of participant assignment until the analysis is complete. During the annual visits to participating general practices, the research team will verify any GP staffing changes. If a GP transfers from an intervention to a control practice or vice versa, their participation will be discontinued to avoid contamination.

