### Data analysis

#### Clinical effectiveness

We will present descriptive statistics to summarise and compare baseline characteristics of GPs and children between the intervention and control groups. The primary analysis will be on an intention-to-treat basis, i.e. based on the randomised group allocation of the children’s GP practice, regardless of the actual care received. Additionally, a per protocol analysis will be performed, including only children in the intervention group who received the diagnostic strategy and CRP POCT as intended, and children in the control group who did not undergo CRP-testing.

Analyses will be carried out on the individual patient level. Dichotomous outcomes (proportions) will be analysed using logistic mixed-effect regression models with fixed effects for group allocation and practice size, and a random effect for practice to account for clustering of patients within GP practices. Continuous outcomes will be analysed using linear mixed effects regression models with the same approach. When outcomes are measured repeatedly, an additional random effect for patient will be included to account for within-patient correlation, along with fixed effects for time and, if appropriate, its interaction with allocation. If necessary, fixed effects for clinically meaningful differences in baseline characteristics will be included in supplementary analyses. Exploratory analyses will be performed to assess subgroup differences in effectiveness by age and sex through inclusion of the corresponding treatment-by-subgroup interaction terms in the regression models.

Estimates of intervention effects ((adjusted) mean differences or ORs, as appropriate) are presented with 95% confidence intervals (CIs). Adverse health outcomes (e.g. complications in appendicitis cases and non-appendicitis cases, missed other emergency diagnoses) will be summarised descriptively, without further statistical analysis.

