Still, our study has some limitations. First, although the cluster design reduces potential contamination between GPs [74, 75], it can introduce selection bias if GPs in the intervention arm include children with different characteristics (e.g. more severe symptoms) than those in the control group [76]. To address this, missed eligible children are identified retrospectively via GP registries, and their characteristics compared with those of included children for both groups, with adjusted analyses conducted if baseline differences are observed. Second, GPs and patients are not blinded, which may lead to bias. However, we consider this bias to be limited, as pragmatic trials assess overall effects on the care pathway rather than isolated intervention effects [27]. Third, children presenting at out-of-hours primary care service are not included because of logistical constraints related to the inclusion of GPs and children at these services, particularly the training of an unfeasibly large number of GPs and the reviewing of medical records at numerous individual practices within the service’s catchment area. This may limit generalizability of findings to out-of-hours settings due to potential differences in urgency and severity of appendicitis.

In summary, this study will evaluate whether a diagnostic strategy for appendicitis in children presenting to their GP with acute abdominal pain can reduce referrals to secondary care without increasing delayed diagnoses, compared to usual care. If our hypothesis is confirmed, the findings may support its adoption in routine practice, ultimately contributing to more efficient care and better outcomes for these children.

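### Age and sex should be prespecified in the primary model; covariate adjustment is now only supplementary and triggered by observed imbalance

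*Protocol article*

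**What the plan says.** The Clinical effectiveness section of the protocol article analyses dichotomous outcomes, which include the primary outcome, with "logistic mixed-effect regression models with fixed effects for group allocation and practice size, and a random effect for practice". No patient-level term appears. On other covariates it says: "If necessary, fixed effects for clinically meaningful differences in baseline characteristics will be included in supplementary analyses". The Discussion, on selection bias, gives the same trigger: "with adjusted analyses conducted if baseline differences are observed". Age and sex appear in the analysis section only as exploratory treatment-by-subgroup interactions.

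Three statements about design bear on this:

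- Allocation is by practice: "GP practices are randomly allocated to the intervention or control group using computer-generated 1:1 permuted-block randomisation", stratified by practice size only.
- Enrolment is by the clinicians in those practices: "Participating GPs and GP trainees will recruit eligible children during office-hour consultations".
- Masking is absent at that level: "Blinding of GPs and patients is neither feasible nor appropriate in this pragmatic study".

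The Discussion accepts that GPs in the two arms may include different kinds of children and gives more severe symptoms as the example. Its answers are a retrospective search for missed eligible children, a comparison of those children with the included ones in both groups, and the conditional adjusted analyses. The Recruitment section has GP assistants run the search monthly.

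Age and sex are easy to obtain. The Fig. 3 legend says that for eligible children who do not take part, "Anonymised baseline data (age, sex, date of baseline consultation, and randomisation group) will be collected". Male sex scores 2 points in the prediction rule (Table 1); age is not an item.

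**The concern.** Two features combine. First, adjustment depends on what the baseline table shows. A variable enters because the arms happen to differ on it, not because it predicts referral. A strong predictor with a small imbalance may be left out, and a weak one with a large imbalance brought in. Second, adjusted results stay supplementary, so the primary estimate takes no account of patient characteristics however the arms turn out.

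In an individually randomised trial with concealed allocation this would matter little, because imbalance would be chance. Here the children are enrolled after allocation by GPs who know the arm, so some imbalance may be systematic, and the protocol says so. At stake are a small, removable part of any such bias and possibly a little precision.

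**Working it through.** **1. The protocol's sample size.** Inputs from Sample size considerations: efficiency 88% and 95%, two-sided 5%, 80% power, cluster size 3, intraclass correlation 0.01.

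- Pooled two-proportion formula: (1.96 × √(2 × 0.915 × 0.085) + 0.842 × √(0.88 × 0.12 + 0.95 × 0.05))² / 0.07² = 248 per arm.
- Design effect: 1 + (3 − 1) × 0.01 = 1.02; 248 × 1.02 = 253 per arm.
- In whole practices of 3: 85 × 3 = 255 per arm, as stated. 255 / 0.9 = 283.3, stated as 283.
- Effective size 255 / 1.02 = 250 per arm; power 80.3%.
- Expected referrals among children without appendicitis: 255 × 0.12 + 255 × 0.05 = 30.6 + 12.75 ≈ 43.

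The figures reproduce. The change proposed here does not alter them.

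**2. Effect of a sex imbalance on the unadjusted estimate.** Assumptions, since the documents give none: 50% boys, a sex log odds ratio for referral of 0.6, overall referral 12%.

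- Solving for the intercept gives referral of about 15.1% in boys and 8.9% in girls; the difference is 6.2 points.
- A 5-point difference in the share of boys shifts efficiency by 0.05 × 6.2 = 0.31 points. 0.31 / 7 = 4% of the planned effect.

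Over a wider assumed range (imbalance 5 to 10 points, sex odds ratio 1.5 to 3, excess of boys in the intervention arm), the normal approximation at 250 effective children per arm gives:

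| Quantity | No imbalance | Smallest | Largest |
|---|---|---|---|
| Referral odds ratio when the true effect is nil | 1.00 | 1.02 | 1.10 |
| Type I error | 5% | 5.1% | 6.6% |
| Power for 88% to 95% | 80.3% | 79.0% | 73.4% |

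An excess of boys in the control arm would push the estimate the other way.

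**3. Power with age and sex in the model, no selection.** Both results are logistic simulations of 1,500 runs with 255 children per arm. In the second, 170 practices of 3, an intraclass correlation of 0.01 and cluster-robust standard errors stand in for the mixed model.

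- Assumed sex log odds ratio 0.6 and age log odds ratio 0.5 per standard deviation: 80.3% without the covariates, 82.2% with them.
- Assumed sex odds ratio 1.5 and no age effect: 80.5% without, 80.5% with. Type I error 5.6% and 5.8%.

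Monte Carlo error for a power near 80% is √(0.8 × 0.2 / 1,500) ≈ 1 point. The gain is therefore about 0 to 2 points, and neither scenario shows a loss.

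**4. Selection by severity.** Same simulation as the second one above. Assumptions: 20% of children severe, odds ratio 6 for referral, a 10-point excess of severe children in the intervention arm, no true effect.

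| Model | Odds ratio (true value 1) | Rejection rate |
|---|---|---|
| Allocation only | 1.24 | 12.3% |
| Plus age and sex | 1.24 | 12.5% |
| Plus age, sex and severity | 1.00 | 4.6% |

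Age and sex leave this bias where it was.

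**The case against.** The strongest reply is that the primary analysis is already prespecified and includes the only stratification factor: "fixed effects for group allocation and practice size, and a random effect for practice to account for clustering". Conditional choice touches only analyses labelled supplementary. That stands. A reader might infer that the primary estimate itself is data-driven, or that nothing says which estimate carries the conclusion. The text does not support this, because calling the adjusted analyses supplementary ranks them. Analysts are also to be blinded to allocation until the analysis is complete, which limits steering of covariates towards a result.

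A reader might also expect a large bias. A trait with 36% against 6% referral, held by 20% of children, would shift efficiency by 0.05 × 30 = 1.5 points per 5-point imbalance, or 21% of 7. But its odds ratio is (0.36/0.64) / (0.06/0.94) ≈ 8.8. That describes something like severity. Nothing in the documents supports it for age or sex.

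The evidence for the two covariates is limited. Sex is an item of a rule that predicts appendicitis. It feeds the advice in the intervention arm, but the documents do not show that it predicts referral of children without appendicitis under usual care. They link age to referral nowhere. The power gain therefore rests on assumption.

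The record search and the comparison with missed children are real safeguards. They are partial: missed children must still agree to take part, and a comparison does not change the estimate.

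A full covariate list may be left to the analysis plan. The trigger, however, is stated in the article and can be judged as written.

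**Conclusion.** The point holds as a nearly free improvement, not as an error that endangers the trial. The rule ties covariate choice to observed imbalance, in a design where enrolment follows allocation and is unblinded, and the primary model omits two patient variables that are already collected.

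The expected benefit is about 0 to 2 points of power and, under the assumed sex effect and 50% boys, removal of about 0.3 points of efficiency bias per 5-point sex imbalance. These sizes rest on assumed covariate effects.

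A reader might infer that adding age and sex cures the selection bias described in the Discussion. It does not: in the simulation the null odds ratio stays at 1.24 with or without them. Whether severity can be handled depends on data that cannot be checked here. The baseline form includes the strategy, and so the rule items, only for the intervention group, and the contents of the standardised medical record form (Supplementary 7) are not shown.

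**What to change.** - Prespecify the primary model as allocation, practice size, age and sex as fixed effects with a random practice effect, whatever imbalance is seen. Fix the form in which age enters.
- Report the model without age and sex as a sensitivity analysis.
- Remove both triggers: the necessity condition in the Clinical effectiveness section and the observed-difference condition in the Discussion.
- State that the odds ratio is conditional on these covariates. Adding covariates to a logistic model changes the quantity estimated even without imbalance, so the two models' odds ratios are not strictly comparable.
- Keep a prespecified supplementary analysis that adds named severity items, only if they are recorded in the same way in both arms. If they are not, say that this selection cannot be adjusted for.
- Retain the monthly search and the comparison with missed children.
- Do not add availability of a CRP device as a covariate unless it is recorded before allocation; the protocol does not say when it is recorded.

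The cost is a few sentences before the analysis begins; inclusion is expected to run to January 2028. The primary model gains two parameters if age enters linearly, against about 43 expected referrals. No new data and no change in sample size are needed.

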#### Cost-effectiveness

Cost-effectiveness will be calculated from both a societal (including productivity loss) and a health care perspective with a time horizon of 30 days. Secondary analyses will address a 3-month time horizon. Both cost-effectiveness and cost-utility analyses will be performed to compare the ratio of costs and effects between arms. In the cost-effectiveness analysis, incremental cost effectiveness ratios will be calculated, using efficiency as effect parameter. Cost-utility will be calculated based on the EQ-5D-(Y)-3 L, by which we will determine the added costs per quality-adjusted life year gained. For the EQ-5D-3 L proxy and EQ-5D-Y, utility scores will be derived using the Dutch value set [58]. For the EQ-5D-3 L, the Dolan algorithm will be applied [59]. Bootstrap re-sampling will be performed in order to estimate CIs. Additionally, based on the bootstrap replications, cost-effectiveness and cost-utility planes will be plotted, along with cost effectiveness acceptability curves (CEACs).

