#### Child anxiety

Anxiety in children is assessed using the 20-item Dutch version of the State-Trait Anxiety Inventory for Children (STAIC) at 30 days and 3 months follow-up. The Dutch version of the STAIC (Zelfbeoordelingsvragenlijst voor Kinderen (ZBV-K) Versie Nu) measures self-perceived anxiety based on the state-anxiety subscale and is feasible for children ≥ 8 years. The Dutch version of the state-anxiety subscale has demonstrated good validity and reliability in children (Cronbach’s alpha 0.80 or higher) [45].

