#### Child’s quality of life

Quality of life will be evaluated at 30 days and 3 months follow-up using the EuroQol 5D 3 L (EQ-5D-3 L), a generic instrument measuring health-related quality of life (HRQOL). The EQ-5D-3 L includes five domains (mobility, self-care, usual activities, pain or discomfort and anxiety or depression) that are each rated on a three-level severity scale (0 = no problems, 1 = some problems, 2 = extreme problems). The EQ-Visual Analogue Scale records the child’s overall health status with scores ranging from 0 to 100. Parents will complete the EQ-5D-3 L proxy for children aged ≤ 7 years. Children aged 8–15 years will complete the EQ-5D-youth (EQ-5D-Y) and children ≥ 16 years will complete the EQ-5D-3 L. The EQ-5D-Y is highly feasible for assessing HRQOL in children and adolescents with different health conditions [48–51]. Additionally, it has good convergent validity and fair to moderate test-retest reliability (test-retest agreement 70–99%) [49, 51].

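### The 30-day cost per QALY rests on a starting utility that is never measured, because the EQ-5D is first collected at day 30

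*Protocol article*

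**What the plan says.** The Cost-effectiveness section sets the main horizon: "Cost-effectiveness will be calculated from both a societal (including productivity loss) and a health care perspective with a time horizon of 30 days". A longer horizon is secondary: "Secondary analyses will address a 3-month time horizon". Two ratios are planned. The cost-effectiveness ratio uses referral efficiency as its effect. The cost-utility ratio uses the EQ-5D, from which "we will determine the added costs per quality-adjusted life year gained". Bootstrap intervals, planes and acceptability curves follow.

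The section on the child's quality of life fixes the measurement times: "Quality of life will be evaluated at 30 days and 3 months follow-up". Table 2 agrees, with marks at 30 days and 3 months and none at baseline. The Data collection section agrees too: questionnaires go out at those two times only, and the baseline case report form covers eligibility, contact details, CRP testing and referral, plus the diagnostic strategy in the intervention arm. No section gives a starting utility, a retrospective rating or a rule for the first 30 days.

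**The concern.** A QALY is utility accumulated over time. Over the main horizon each child contributes one utility value, at the closing end. The area under the curve then depends on a starting value that nobody measures.

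The unmeasured window is the one that matters most. Children enter with abdominal pain of at most 7 days (Study population), more than 90% have self-limiting conditions (Background), and the strategy acts on decisions made the same day or the next morning (Intervention section). Pain, referral and admission therefore fall mostly before the first EQ-5D.

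Cost-effectiveness is one of the trial's three stated aims. If both arms have largely recovered by day 30, the QALY difference will mainly reflect noise and the assumed starting value. The cost-utility plane and acceptability curve would then look more informative than the data behind them.

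**Working it through.** The article states no QALY figure, so there is nothing to reproduce. The check asks what the planned schedule can deliver.

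**Inputs from the article.** Main horizon 30 days; secondary horizon 3 months (about 91 days); EQ-5D at day 30 and month 3 only.

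**Assumed inputs.** Day-30 utility u30 = 0.95; starting utility u0 varied; utility losses and durations as shown below.

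**1. Size of the horizon.** 30/365.25 = 0.0821 QALY at most per child.

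**2. Dependence on the starting value.** By the trapezoid rule, QALY(0–30) = 0.0821 × (u0 + u30)/2. With u30 = 0.95:

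| Assumed u0 | 30-day QALY |
|---|---|
| 0 | 0.0821 × 0.475 = 0.039 |
| 0.3 | 0.0821 × 0.625 = 0.051 |
| 0.5 | 0.0821 × 0.725 = 0.060 |
| 0.7 | 0.0821 × 0.825 = 0.068 |
| 0.95 | 0.0821 × 0.95 = 0.078 |

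The unmeasured input moves the result by a factor of two.

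**3. What the usual substitutes do to the arm difference.**
- A common u0 in both arms gives a difference of 0.0821/2 × (difference in u30).
- Carrying u30 back to day 0 gives 0.0821 × (difference in u30).

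Under either choice, a difference between arms during the acute phase enters only if it is still visible at day 30.

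**4. Size of what could be lost.** Suppose the arms differ by 1 to 7 days in an acute state with a utility loss of 0.2 to 0.6. The true difference per child is then between 0.2 × 1/365.25 = 0.0005 and 0.6 × 7/365.25 = 0.0115 QALY. If both arms have the same utility at day 30, neither substitute shows any of it.

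**5. The 3-month horizon.** Days 30 to about 91 lie between two measurements: (91.3 − 30)/91.3 = 67% of the span. The first 30 days, 30/91.3 = 33%, have the same gap.

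**6. Why the timing of an early point matters.** Take u0 = 0.5 and u30 = 0.95. A straight line between them implies a loss of 0.0821 × 0.45/2 = 0.0185 QALY. A loss of 0.45 that lasts 7 days and then ends is 0.45 × 7/365.25 = 0.0086. The same two values give a loss about twice as large under one path as under the other, so an early value needs its date.

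**The case against.** Four points can fairly be made for the plan.

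*A number can be produced.* A reader might infer that the 30-day QALY cannot be computed at all. That goes too far: an assumed starting utility with sensitivity analysis yields a figure, and a health-economic analysis plan could specify one. What stands is narrower. The result would come from an assumption the article does not state, and no later plan can recover acute-phase utilities that were not collected.

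*Some effects may last.* A reader might also infer that the whole effect is unobserved, or that the QALY difference must be near zero whatever the strategy does. The documents do not show this. The Background lists complications of perforated appendicitis, such as abscess, readmission and prolonged hospital stay, that could still lower utility at day 30 or later. Only about 5% of these children have appendicitis, so the contribution is probably small, but it is not nil. This is why the result is called largely, not wholly, insensitive.

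*The recall period is not stated.* That the EQ-5D rates health at the time of completion is an assumption here, since the article gives no recall period. An instrument that covered the preceding month would narrow the gap.

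*The damage is limited.* The primary outcome and safety come from medical records. Costs come from medical records and questionnaires, and the cost-effectiveness ratio uses efficiency. All of these stand.

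**Conclusion.** The point holds for the cost-utility analysis only. The article sets a 30-day main horizon and collects no utility before day 30; three places in the text agree on that schedule, so this is not a detail left to another document. The 30-day QALY is not identifiable from the collected data. Under an assumed day-30 utility of 0.95 it can lie anywhere from 0.039 to 0.078, depending on the starting value. It is largely insensitive to the acute episode, and the 3-month analysis shares the gap for about a third of its span. The conclusion rests on the EQ-5D describing current health and on most acute loss having passed by day 30, which fits the study population described.

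One side remark. The Child anxiety section plans the "State-Trait Anxiety Inventory for Children (STAIC) at 30 days and 3 months follow-up", using the Dutch 'now' version of the state subscale. Given first at day 30, it cannot show anxiety around the referral. The protocol is consistent on this, so it is a limit on interpretation and adds nothing to the weight of the QALY point.

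**What to change.** 1. **Children still to be enrolled.** Send a short REDCap EQ-5D immediately after consent, because consent is what covers questionnaires. Record the completion date and the days since the consultation.
2. **Use of that value.** Enter it as an early point in the area under the curve, and state what is assumed between the consultation and that point. Do not use it as a pre-treatment covariate. Consent follows allocation and the referral decision, non-responders are phoned only after seven days, and the record search for missed children is monthly. The answer is therefore post-intervention, and adjusting for it could remove the effect being sought.
3. **Children already enrolled or found late.** State the assumed utility path over days 0 to 30 and vary it in sensitivity analyses.
4. **If no early measurement is added.** Do not present the 30-day cost per QALY as a main result. Report costs against efficiency, and label any QALY result as assumption-based and insensitive to the acute phase.
5. **Anxiety.** Add the state scale to the same early questionnaire for children aged 8 or over, or limit the anxiety conclusion to day 30 and later.

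The cost is a small amendment and a few extra questions per family. Enrolment began in March 2025 and is expected to run to January 2028, so early values will be missing for children already in the trial. Option 4 costs only wording.
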